**Results::**

We will evaluate the preliminary efficacy of the apps via post-intervention group differences on the validated 18-item Prostate Cancer Knowledge Scale (primary outcome). We will also explore post-intervention group differences in perceived engagement, accessibility, and acceptability between the apps. Finally, we will derive preliminary estimates of PSA screening rates between study conditions and identify mechanisms of screening adherence.

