### Study randomization

2.3.

Participants (*N* = 80) will be assigned using stratified randomization to one of two study conditions: the Taskforce App (*n* = 40) or the Genius App (n = 40). Participants will be stratified on family history of prostate cancer (yes/no) and reading level (> 8th grade vs. ≤ 8th grade; based on scores on the Rapid Estimate of Adult Literacy in Medicine – Short Form [37]) to ensure that both study conditions are balanced on important factors associated with prostate cancer knowledge and screening [38–41]. An online baseline survey will be administered before randomization, and a post-intervention survey will be administered immediately after the intervention.

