#### Secondary outcomes

2.10.2.

Imaware^™^ will share information about PSA results with our research team to allow for the calculation of test completion rates. Participants have 30 days to order a PSA test kit. Perceptions of how engaging the app will be measured during the post-intervention assessment using the User Engagement Scale (UES) [58], which is a 31-item multidimensional scale measuring six distinct dimensions of (a) aesthetic appeal, (b) focused attention, (c) novelty, (d) perceived usability, (e) felt involvement and (f) endurability. The System Usability Scale (SUS) [59] will measure *perceived accessibility*, a 10-item bidimensional scale of (a) how useable and (b) how learnable the app was.

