### Analytical plan

2.12.

We will assess pre-post intervention group differences on the Prostate Cancer Knowledge Scale using a two-sample *t*-test. Linear regression will also be used to estimate the post-intervention difference on the Prostate Cancer Knowledge Scale while accounting for the participant’s baseline score on the Prostate Cancer Knowledge Scale and demographic and psychosocial characteristics (e.g., age, insurance status). We anticipate that the participant characteristics, family history of prostate cancer, and literacy level will be well balanced by randomization. However, we will examine the potential moderating effect of these variables on pre-post group differences in the Prostate Cancer Knowledge Scale.

PSA screening test rates will be calculated for (1) the overall screening rate across both groups and (2) Taskforce App vs. Genius App. A chi-square test of independence (or Fisher’s exact test, as appropriate) will be used to compare PSA screening test completion rates between study conditions. We will also examine between-group differences (Taskforce App vs. Genius App) at follow-up through the overall score of UES and each of the six dimensions using two-sample *t*-tests. For perceived accessibility, we will also use two-sample t-tests to explore between-group differences, as measured via the overall score of SUS.

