## Discussion

4.

Prostate cancer is the most diagnosed cancer in AA men and the second‑leading cause of cancer-related deaths [64–66]. The current pilot study will test the first-of-its-kind mHealth app to improve prostate cancer knowledge and increase PSA screening uptake among AA men using home-based screening methods. The Genius App is theory-driven and community-guided, offering culturally tailored education about prostate cancer for AA men. Our primary hypothesis is that participants randomly assigned to the Genius App will report significantly greater knowledge on the Prostate Cancer Knowledge Scale post-intervention than participants randomly assigned to the Taskforce App. We will also derive preliminary estimates of the effects of each prostate cancer screening app on at-home PSA screening test completion rates.

This study has many notable strengths. First, it focuses on a high-risk group with a limited history of prostate cancer screening, concentrating on an important public health disparity [64]. Second, it addresses many of the methodological limitations of existing prostate cancer screening app pilot studies through a rigorous experimental design [24,67]. Third, via weekly smartphone assessments, the study will measure mechanisms of behavior change, including the cognitive and emotional changes that individuals go through when engaging with a longitudinal cancer screening intervention that is otherwise not collected in standard screening interventions. Fourth, the remotely delivered, culturally responsive intervention addresses both patient-level factors (i.e., equitable access to screening) and structural-level factors (i.e., equitable access to culturally tailored information for AA men) that disproportionately affect AA men [68–71].

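### PSA completion is meant to be estimated, but the only between-arm analysis named is an unstratified chi-square or Fisher test; lead with a risk difference and 95% CI

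*Protocol article*

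**What the plan says.** The Abstract (Results) states the aim for this outcome: "we will derive preliminary estimates of PSA screening rates between study conditions". The Discussion goes from rates to effects; the authors will "derive preliminary estimates of the effects of each prostate cancer screening app on at-home PSA screening test completion rates".

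Section 2.12 (Analytical plan) starts with description: "PSA screening test rates will be calculated for (1) the overall screening rate across both groups and (2) Taskforce App vs. Genius App". For the comparison of the arms it then names a chi-square test of independence, or Fisher's exact test where appropriate, "used to compare PSA screening test completion rates between study conditions". It names no risk difference, ratio or interval for this outcome. For knowledge, by contrast, the same section uses linear regression to estimate the post-intervention difference.

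Two other places matter. Section 2.3 says "Participants will be stratified on family history of prostate cancer (yes/no) and reading level", with 40 men per arm. Section 2.10.2 says the kit company shares PSA results with the research team "to allow for the calculation of test completion rates", so kit completion does not depend on the post-intervention survey.

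**The concern.** An estimation aim and a hypothesis test answer different questions. Someone designing the follow-on trial needs to know how large the difference in completion may be and how uncertain that figure is. A p-value gives neither. With 40 men per arm, a difference worth pursuing can easily miss significance, and a report led by the test would then read as if no effect had been found.

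The test also makes no use of family history and reading level, although the design balances on both because the authors link them to knowledge and screening. This is a smaller point: it affects efficiency, not validity.

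**Working it through.** **The article's own figure.** The only power statement (section 2.11) concerns the knowledge scale: SD 3.1, difference 2.3, 30 per group, two-sided alpha 0.05. The standardised difference is 2.3/3.1 = 0.742. Power is 0.82 by the normal approximation and 0.81 by the noncentral t, so the stated 80% reproduces. No rate, power or precision is stated for PSA completion.

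**Inputs for PSA completion.** n = 40 per arm (section 2.3). Two-sided alpha of 0.05 is borrowed from the knowledge calculation. Control rates of 10% to 40% are my assumption.

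**Power of the named tests.** For each pair of true rates, the binomial probabilities of all tables with 40 men per arm that give p ≤ 0.05 are summed (chi-square without continuity correction):

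| Assumed Taskforce vs Genius | Chi-square | Fisher |
|---|---|---|
| 10% vs 30% | 63% | 53% |
| 20% vs 40% | 50% | 41% |
| 30% vs 50% | 46% | 37% |
| 40% vs 60% | 46% | 37% |
| 30% vs 60% | 80% | 72% |

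By the normal approximation, with control rates from 10% to 50%, power is 14% to 24% for a 10-point difference and 78% to 89% for a 30-point difference. For 80% power, 30% versus 50% would need 93 men per arm.

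**What each analysis would report.** Suppose 12/40 complete a test with Taskforce and 20/40 with Genius.

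- Test: the pooled rate is 32/80 = 0.40, so z = 0.20 / √(0.40 × 0.60 × 2/40) = 0.20/0.1095 = 1.83 and p = 0.068. Fisher gives p = 0.110.
- Estimate: the difference is 0.50 − 0.30 = 0.20. The Wilson 95% limits are 0.352 to 0.648 for 20/40 and 0.181 to 0.454 for 12/40. The Newcombe limits are:
  - lower: 0.20 − √[(0.500 − 0.352)² + (0.454 − 0.300)²] = 0.20 − 0.214 = −0.014
  - upper: 0.20 + √[(0.648 − 0.500)² + (0.300 − 0.181)²] = 0.20 + 0.190 = 0.390

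The result is 20 points, 95% CI −1.4 to 39.0.

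**Expected precision.** The approximate half-width is 1.96 × √[p₁(1−p₁)/40 + p₂(1−p₂)/40]. For a 20-point difference this is 17 points at 10% vs 30%, 21 at 30% vs 50% and 21.5 at 40% vs 60%. The maximum, with both rates at 50%, is 1.96 × √(0.5/40) = 22 points.

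**The case against.** The strongest reply is that the promised estimates are already planned. Section 2.12 calculates the rate in each arm before it names any test, and two rates with their denominators let anyone work out a difference and an interval. The article is condensed, and an unseen SAP may name an interval, a denominator and an adjustment. PSA completion is a secondary outcome in a declared pilot, so low power for it is not an error.

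Much of this stands. A reader might infer three stronger things that the article does not support:

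- **That no estimate is planned, or that the test is uninformative.** The arm rates are planned, and the test has about 80% power for differences near 30 points. What the stated comparison lacks is an effect measure with its precision.
- **That ignoring the strata invalidates the comparison.** An unstratified test after stratified randomisation is valid and usually slightly conservative. With two binary factors there are four strata, on average 80/4 = 20 men each, so adjustment may meet sparse cells.
- **That rates will be computed among survey completers only.** Nothing says so. The 60 men in section 2.11 belong to the knowledge calculation, and the data source in section 2.10.2 points towards all randomised men.

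What remains does not rest on a missing detail. The Abstract and Discussion state an estimation aim, section 2.12 states a test as the comparison, and a method that serves the aim better costs almost nothing.

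**Conclusion.** The point holds as a cheap improvement, not as an error of validity. The named between-arm analysis does not deliver what the Discussion promises, namely preliminary estimates of effect with enough information to plan from. At 40 per arm the named tests have about 37% to 63% power for a 20-point difference, with the lower values from Fisher and the highest from chi-square at a 10% control rate. For 30% versus 60% they have about 72% to 80%. A non-significant result would therefore not exclude a useful difference. An interval with a half-width of about 17 to 22 points shows this directly. All of these figures rest on assumed completion rates and a two-sided 5% level, because the article gives neither for this outcome.

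**What to change.** Change the PSA paragraph of section 2.12, or confirm that the SAP already says this:

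1. Make the main PSA result the risk difference, Genius minus Taskforce, with a 95% CI, among all randomised men.
2. Preferably adjust for family history and reading level, for example with a Mantel-Haenszel risk difference, and fall back to an unadjusted Newcombe interval if strata are sparse.
3. Keep the chi-square or Fisher p-value as supportive.
4. For the at-home kit endpoint, count men with no kit result from the company as not completed. Report clinic tests separately: they are self-reported in the app (section 2.5.2.3), so the same rule could misclassify men who were tested in clinic but did not report it.

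The cost is one or two sentences and no new data. The small downsides are an interval that is visibly wide and possible sparse strata, which the fallback covers.

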#### Qualitative data analysis

2.12.1.

Recordings from exit interviews will be transcribed and then loaded into NVivo [61] (Version 12) for analysis. An inductive thematic approach will inform the qualitative analysis [62,63]. The investigative team (led by [name]) will create the codebook and then code two interviews as a team, which will be used to revise the codebook (if needed). Once consensus has been reached on coding, the coded transcripts will be reevaluated, and themes will be identified within and across codes. These themes will highlight the study apps’ strengths and weaknesses, providing insight into improving acceptability and the participant experience.

## Results

3.

Data collection is expected to finish in September 2024, and primary and secondary data are expected to be analyzed in Fall 2024, with papers on these anticipated data starting in late 2024 and early 2025.

## Discussion

4.

Prostate cancer is the most diagnosed cancer in AA men and the second‑leading cause of cancer-related deaths [64–66]. The current pilot study will test the first-of-its-kind mHealth app to improve prostate cancer knowledge and increase PSA screening uptake among AA men using home-based screening methods. The Genius App is theory-driven and community-guided, offering culturally tailored education about prostate cancer for AA men. Our primary hypothesis is that participants randomly assigned to the Genius App will report significantly greater knowledge on the Prostate Cancer Knowledge Scale post-intervention than participants randomly assigned to the Taskforce App. We will also derive preliminary estimates of the effects of each prostate cancer screening app on at-home PSA screening test completion rates.

This study has many notable strengths. First, it focuses on a high-risk group with a limited history of prostate cancer screening, concentrating on an important public health disparity [64]. Second, it addresses many of the methodological limitations of existing prostate cancer screening app pilot studies through a rigorous experimental design [24,67]. Third, via weekly smartphone assessments, the study will measure mechanisms of behavior change, including the cognitive and emotional changes that individuals go through when engaging with a longitudinal cancer screening intervention that is otherwise not collected in standard screening interventions. Fourth, the remotely delivered, culturally responsive intervention addresses both patient-level factors (i.e., equitable access to screening) and structural-level factors (i.e., equitable access to culturally tailored information for AA men) that disproportionately affect AA men [68–71].

As with any study, however, there are some limitations. First, the investigative team rigorously controls access to the app to better understand its use during the pilot study. Multiple steps are required (e.g., verbal consent, signing a HIPAA waiver, and completing an activation assessment to ensure the app is downloaded correctly), and all participants must use a study-provided phone. Smartphone ownership is high across socioeconomic status, but the quality of smartphones varies greatly [23]. To ensure access to the app is equitable and functions correctly, study phone use was deemed necessary. Future studies that test the app will not require a study phone unless participants request a phone. Second, although the weekly smartphone assessments offer an important theoretical contribution by exploring mechanisms of behavior change, they may have a small intervention effect by reminding participants to screen in the control group. Despite these limitations, a successful demonstration of the preliminary efficacy of the Genius App will support a statewide effectiveness trial and integration across the OU Health medical system.

## Figures and Tables

**Fig. 1. F1:**
[figure not shown]
Conceptual diagram for Prostate Cancer Genius App.

**Table 1 T1:** Overview of App Features by Study Condition.

App Features	Prostate Cancer Genius App	Taskforce App
*App Instructions*	X	X
*USPSTF Companion App*		
Generic information about prostate cancer and screening	–	X
*Read the Prostate Cancer e-Book*		
Culturally tailored information about prostate cancer and screening.	X	–
*Watch Videos about Prostate Cancer*		
Experience sharing from AA prostate cancer survivors.	X	–
*Talk with a Prostate Cancer Survivor*		
Schedule a call and select a topic to talk with a local AA prostate cancer survivor.	X	–
*Order a Home-Based PSA Test Kit*		
imaware^™^ PSA test kit mailed to home with return mailer.	X	X
*Report My PSA Test Results*		
Participants can report imaware^™^ or a clinic-based PSA test result completed during the study.	X	X
*Track My Rewards*		
Displays the amount of compensation received for completed study assessments.	X	X
*Report a Problem*		
Email the study team if the app isn’t functioning	X	X

**Table 2 T2:** Overview of learning modules in the Prostate Cancer Genius app.

Week*	Module	Educational Content
1	1 2	Introducing prostate cancer The risk of prostate cancer for the AA community
2	3 4	Screening methods and recommendations for prostate cancer How to communicate with healthcare providers about prostate cancer screening
3	5 6	How to complete the at-home PSA test Prostate biopsy exam and results interpretation
4	7 8	How to seek social support from friends and family; The power of faith Masculinity and manhood in making decisions on prostate cancer screening

* *Note.* Two learning modules become available each week, and once presented, they can be accessed on demand.

**Table 3 T3:** Overview of topics for testimonial videos and conversations with prostate cancer survivors.

Watch Videos about Prostate Cancer Topics	Talk With A Prostate Cancer Survivor Topics*
1. AA men who have survived prostate cancer.	1. Family history and warning signs of prostate cancer.
2. How to make faith-based decisions about prostate cancer.	2. Taking the PSA test or the DRE exam.
3. Does getting prostate cancer change your definition of manhood and masculinity.	3. Talking with the doctor about prostate cancer.
4. Knowing the signs and symptoms of prostate cancer.	4. Getting a prostate biopsy.
5. How friends, loved ones, and your community can support your health decisions.	5. Deciding which type of treatment is best for prostate cancer.
6. How you can take action to detect cancer early.	6. What it is like to be a prostate cancer survivor?
7. The benefits and costs of prostate cancer treatment.	7. How does prostate cancer affect your family and friends? 8. How has your life been affected by the side effects of treatment? 9. How has prostate cancer affected you mentally? 10. How has prostate cancer affected you spiritually? 11. Family history and warning signs of prostate cancer.

* *Note.* Participants select from a list of topics they want to speak to a survivor about. The survivor is informed of the participant’s preferred topic before they make the call. Multiple topics can be selected.

**Table 4 T4:** Overview of scheduled assessment and menu options available in both study apps.

Name of Assessment	Brief Description	Assessment Type	Study Condition		Time Window
			TaskForce App	Genuius App	
Welcome Message	An assessment that provides an overview of the assigned study app and its associated features.	Scheduled Assessment^a^	X	X	Day 1 at the preferred assessment time.
Closing Message	An assessment that outlines the remaining steps needed to finish study participation	Scheduled assessment^a^	X	X	Day 30 at the preferred assessment time
Weekly Smartphone Assessment	This is a weekly assessment that assesses the frequency of app use, satisfaction with assigned app content, knowledge and perceptions of prostate cancer screening, readiness to complete a PSA test, and current emotional states.	Scheduled assessment^a^	X	X	Days 7, 14, 21, and 28 at the preferred assessment time
Home-Based PSA Test Reflection Assessment	This assessment measures the thoughts and feelings participants are experiencing while waiting for their results.	Scheduled Assessment^a^	X	X	Triggered 48 h after ordering a PSA test kit. Sent once per day at preferred assessment time until fully completed.
Prostate Cancer Survivor Introduction	An assessment that provides a brief introduction for all the prostate cancer survivors who provided testimonial videos and are participating in the app as “health coaches.”	Scheduled Assessment^a^	–	X	Day 2 at the preferred assessment time
Call A Survivor Check-In	An assessment that provides an opportunity for participants to schedule a conversation with a prostate cancer survivor.	Scheduled Assessment^a^	–	X	Days 5, 12, 19, and 26 at the preferred assessment time
Home-based PSA-Test Check-In	An assessment that provides an opportunity for participants to order a home-based PSA test.	Scheduled Assessment^a^	–	X	Days 3, 10, 17, and 20 at the preferred assessment time
Learning Modules	An assessment that provides an opportunity for participants to complete a learning module on prostate cancer.	Scheduled Assessment^a^	–	X	Days 2, 4, 9,11, 16, 18, 23, and 25 one hour after wake time

a A scheduled Assessment is triggered by the study-provided smartphone. The phone will audibly and visually cue these surveys for 30 s. If a participant does not respond after five prompts, the assessment will be recorded as missed.

**Table 5 T5:** Overview of Domains Across Each Assessment Type.

Descriptive variable	Items	Full Bettery Of Assessments					
		Screener	Enrollment	Baseline	Weekly Smartphone	Post-intervention	Exit Interview
Screening	37	x					
Enrollment [1]	40		x				
Sociodemographic	33			x			
Health Behavior, Mental Health, Physical Health, and Healthcare Provider [2–10]	78			x			
General Cancer Health and Screening [6,11,12]	46			x			
Prostate Cancer Health and Screening [13–18]	78			x			
Psychosocial Factors [4,19–25]	130			x			
Prostate Cancer Health and Screening weekly [13–18]	40				x		
Prostate Cancer Health and Screening Post-Intervention [6,11,13,14,17]	54					x	
Smartphone App Review Questionnaire [26,27]	82				x	x	
Exit Interview	76						x
**Total number of items**	578	37	40	365	39	136	76
**Total time needed to complete the assessment (minutes)**	225 min	10–20 min	30–45 min	60–90 Minutes	10 min per week	30 Minutes	60 min

**Table 6 T6:** Overview Of Qualitative Domains Asked By Study Condition In Exit Interview.

Qualitative Domain	Prostate Cancer Genius App	Taskforce App
1. Overall impressions about study.	X	X
2. Problems encountered while in study or using study phone/app.	X	X
3. Evaluation of culturally tailored app features (e.g., Prostate Cancer e-Book).	X	
4. Reasons why did/didn’t order at-home PSA test kit.	X	X
5. Experience with completing at-home PSA test kit and follow-up navigation	X	X

## Data Availability

No data was used for the research described in the article.
